### Outcomes and assessments

The primary outcome of the study is the clinical pregnancy rate, defined as the probability of successful conception within 12 months from enrolment, whether spontaneous or through assisted reproductive technology. A clinical pregnancy is confirmed by a positive urinary pregnancy test followed by the detection of an intrauterine gestational sac after six weeks of amenorrhea via an ultrasound scan [12]. If an ultrasound scan is not available or inconclusive, the diagnosis of pregnancy will be made clinically. Biochemical pregnancy is not counted as a pregnancy event [27].

The secondary outcome, fecundability, is defined as the probability of conceiving during a normal menstrual cycle with unprotected intercourse [28]. It is measured by the time-to-pregnancy in menstrual cycles, consistent with methodologies described in our previous studies [8, 12, 27]. Specifically, we calculate the interval between the date of the last menstrual period at recruitment (baseline) and before conception (for those who became pregnant within one year) or the last follow-up call (for those who did not conceive or withdrew from the study). This interval is then converted into menstrual cycles by dividing by the average cycle length. The number of months attempting to conceive prior to study entry is considered in the computation of time-to-pregnancy. Monthly menstrual and coital histories captured over the study period are used to determine the cycle length and the cycle-at-risk, minimizing the risk of overestimating the number of cycles at risk in the absence of sexual intercourse.

In addition, live birth rates will be tracked as a downstream reproductive outcome through linkage with medical records among participants who achieve clinical pregnancy.

### Statistical analysis plan

We will perform statistical analyses using the Stata Statistical Software. The primary exposure of interest in this study is the change in circadian behavior and metabolic health indicators over the first 3 months of the preconception period. Although the HELMS program continues throughout preconception, pregnancy, and the postnatal period, this initial 3-month interval is pre-specified in TEMPO as the primary exposure window. This interval was selected to allow sufficient time to capture measurable changes in circadian behaviors and metabolic indicators before pregnancy-related changes occur and before substantial loss to follow-up. Accordingly, only participants who complete the 3-month assessment have a fully characterized exposure and are included in the primary analysis, ensuring correct temporal ordering between exposure assessment and subsequent reproductive outcomes.

To investigate changes in circadian behavior and metabolic health indicators between baseline and the 3-month follow-up as exposure variables, the primary analysis will include only participants who have completed the 3-month visit. To identify any potential selection bias, we will compare baseline characteristics between participants included in and excluded from the primary analysis, as well as those recruited into the TEMPO and HELMS studies alone. We will use Pearson’s chi-squared test for categorical variables and either independent t-test or Mann-Whitney U test for continuous variables.

We will examine the associations of changes in circadian behavior and metabolic health indicators with pregnancy rates using modified Poisson regression models. These models will estimate risk ratios and 95% confidence intervals, adjusting for potential covariates identified from the literature and using a directed acyclic graph [6, 12, 29, 30]. Changes in these indicators will be standardized to z-scores to facilitate comparison of the relative impacts of each exposure indicator. These indicators will be treated either as continuous or categorical exposures (e.g. by tertiles or quantiles). Sensitivity analyses will re-evaluate models with spontaneous conception and live birth as the outcomes.

To examine the associations of circadian behavior and metabolic health indicator changes with fecundability, we will use discrete-time proportional hazards models. These models analyze time-to-pregnancy on a discrete scale (number of menstrual cycles-at-risk during active pregnancy attempts), to estimate the hazard ratio of fecundability, termed as the fecundability ratio, along with a 95% confidence interval [31]. Adjustments for potential covariates will be made, similar to those used in the above Poisson regression models [6, 12, 29, 30]. Unlike the hazard ratio for mortality or morbidity where a ratio of < 1 is desirable, a fecundability ratio of < 1 indicates an undesirable outcome which suggests delayed pregnancy. We will account for left truncation by basing our analysis on risk sets for observed cycles at risk, considering only the cycles actively attempted during the study period. For instance, if a participant has been trying to conceive for four cycles at study entry and achieves pregnancy after seven cycles, only the cycles from the fifth to the seventh will be included in the analysis. Participants will be censored in the analysis if they do not conceive after 12 months from recruitment, start fertility treatment, cease trying to conceive, or are lost to follow-up.

To analyze the associations of socio-demographic and lifestyle factors with circadian behavior and metabolic health changes, we will employ multivariable linear regression for continuous outcomes and multinomial logistic regression for categorical outcomes, adjusting for potential covariates. For the assessment of changes in circadian behavior and metabolic health indicators with gene expression levels, we will utilize independent t-tests or Mann-Whitney U test to evaluate differences in gene expression between groups categorized by high versus low health indicators, determined by median thresholds at each time point. Additionally, correlation testing (Pearson or Spearman) will identify associations between these variables and gene expression. Corrections for multiple testing, such as Bonferroni or false discovery rate, will be applied to reduce the Type I error rate.

A secondary, exploratory analysis will include only participants who have not conceived by the 6-month visit to examine long-term trajectories of circadian behavior and metabolic health indicators. We will use group-based trajectory modelling to characterize these changes at baseline, 3-month, and 6-month intervals, anticipating different patterns such as later improvement, worsening, or stability over the period. Each trajectory group will be analyzed for its association with pregnancy rates and fecundability, adjusting for potential covariates.

Missing data will be handled through multiple imputation, creation of a distinct category for the variable, or exclusion of the variable if the missingness exceeds a predefined threshold (> 15%). We will further perform sensitivity analysis by including only complete data in the analysis.

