**Fig. 2 Fig2:**
[figure not shown]
Study workflow and measurements. Baseline, 3-month, and 6-month visits include the administration of questionnaires or diaries, physical measurements, and blood tests. Participants track their frequency of sexual intercourse, menstrual periods, sleep, and activity using a mobile application and digital wearable while trying to conceive. The 9-month visit consists of a phone call where research staff check participants’ pregnancy status and conception attempts if no update received. Throughout the follow-up period, participants with a positive urinary pregnancy test are invited to undergo a dating scan at 6–10 gestation weeks to confirm pregnancies, with outcomes retrieved from medical records. Participants who do not conceive by 12-month will be invited to attend a medical review and referred for fertility medical treatment before withdrawal from the study

At the same visit, each participant receives a digital wearable ‘Oura Ring’ (Oura Health Oy, Finland) for continuous monitoring of sleep and activity. The participants are guided on how to use the HELMS mobile app to track dietary intake, sleep-wake patterns, sexual activity, and menstrual cycles, with a paper diary available as an alternative. Participants are instructed to promptly report any positive pregnancy tests after the baseline visit to schedule an ultrasound confirmation. Physical follow-up visits, which include the same assessments as at baseline, are scheduled at 3-month and 6-month intervals if conception has not occurred, during which conception attempts and family planning decisions are monitored. At 9-month, research staff conduct a follow-up phone call to check on conception attempts and pregnancy status. By 12-month, non-pregnant participants undergo a final health review and are referred for fertility treatment if needed.

Partner assessments are conducted once at the baseline visit during the preconception period to collect socio-demographics, medical history, chrononutrition profile, weight, height, and body fat composition; semen analysis results are retrieved from medical records, if available. Detailed data collection is summarized in Table 1.

**Table 1 Tab1:** Data collection

	Baseline	3-month	6-month	9-month	12-month
Informed consent	√				
Eligibility criteria	√				
Background characteristics^a^					
Socio-demographics	√				
Medical history	√				
Lifestyles					
Alcohol intake and cigarette smoking	√	√ ^b^	√		

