### Sample size

To address the primary aim based on the assumption to detect a medium effect size of 0.4 standard deviation (equivalent to approximately a one-unit change in BMI) in changes of circadian behavior or metabolic health indicators from baseline to 3-month, we calculated that a sample size of 198 females is required. This sample size is supported by findings from previous trials that employed the healthy plate concept or a digital intervention alone, both components of the HELMS intervention, which demonstrated significant reductions in BMI exceeding one unit over a 3-month period [32, 33]. The calculation was based on achieving 80% statistical power and maintaining a two-sided type I error rate of 5%, under the assumption that 50% of the cohort will become pregnant within the year. To account for a potential 30% incomplete 3-month follow-up (including an estimated 15% pregnancy rate within 3 months) and parameter uncertainty, we will enroll a total of 283 participants.

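### Completing the 3-month visit does not ensure that exposure precedes conception: women with an unrecognised early pregnancy could be analysed as exposed and counted as later events

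*Protocol article*

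**What the plan says.** All places are in the protocol article.

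- **Statistical analysis plan.** The exposure is the change in circadian and metabolic indicators from baseline to 3 months. Entry to the primary analysis is defined twice, both times only by completion of the 3-month visit. This is presented as "ensuring correct temporal ordering between exposure assessment and subsequent reproductive outcomes". The section also says the 3-month window was chosen so that changes are captured before pregnancy alters them.
- **Outcomes and assessments.** The clinical pregnancy rate is "defined as the probability of successful conception within 12 months from enrolment". The clock starts at enrolment.
- **Study procedure.** Physical follow-up visits "are scheduled at 3-month and 6-month intervals if conception has not occurred". Participants are told to report a positive test promptly. A dating scan is offered at 6 to 10 weeks of gestation.
- **Table 1.** Pregnancy status is recorded at 3 months. How it is checked is not stated.
- **Sample size.** An estimated 15% pregnancy rate within 3 months is included in the 30% allowed for incomplete 3-month follow-up.
- **Exploratory trajectory analysis.** Entry here does require that the woman has not conceived by the 6-month visit. The primary analysis has no equivalent condition.

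**The concern.** The protocol claims a property, that exposure comes before outcome, which its entry rule does not deliver. Staff can withhold the 3-month visit only when a conception is known, and a conception precedes the positive test that reveals it. A woman in that interval attends, and her weight, body composition, glucose, insulin, lipids, meal and sleep timing and RNA sample are taken while she is pregnant. She then tests positive and is scanned. Because the outcome window opens at enrolment, she is an event.

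For such women the outcome may have influenced the exposure. All of them are events, so any early-pregnancy effect on an indicator enters one side of the comparison only and does not average out. In the gene-expression analysis, pregnancy could move both the indicator and the transcript level and so produce a correlation between them. The planned sensitivity analyses (spontaneous conception, live birth, complete data) do not compare conception date with visit date, so they would not reveal the problem.

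**Working it through.** **1. The plan's own figure.** Inputs from Sample size: "medium effect size of 0.4 standard deviation", "achieving 80% statistical power", two-sided 5% error, and "50% of the cohort will become pregnant within the year", which gives equal groups.

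n per group = 2 × (1.960 + 0.842)² / 0.4² = 98.1, rounded up to 99. The total is 198, with power 80.4%. This matches "a sample size of 198 females is required". Inflation: 198 / 0.70 = 282.9, so 283. Both figures reproduce and are not in dispute. Half of 198 gives about 99 expected pregnancies.

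**2. Conception rate near the 3-month visit.** The article supports three constant monthly hazards:

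- A: 15% in 3 months: −ln(0.85)/3 = 0.0542
- B: 50% in 12 months: −ln(0.50)/12 = 0.0578
- C: 50% of the analysed women over months 3 to 12: −ln(0.50)/9 = 0.0770

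**3. Women pregnant but unaware at the visit.** The article gives no time from conception to recognition, so 2 to 4 weeks is assumed. Fraction f = 1 − exp(−hazard × weeks / 4.345); women = 198 × f.

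| Hazard | 2 weeks | 3 weeks | 4 weeks |
|---|---|---|---|
| A | 4.9 | 7.3 | 9.6 |
| B | 5.2 | 7.7 | 10.3 |
| C | 6.9 | 10.3 | 13.6 |

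The range is about 5 to 14 women, which is 4.9/99 = 5% to 13.6/99 = 14% of the pregnancies.

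**4. Effect on the contrast.** On the scale used for the sample size (mean change, pregnant minus non-pregnant), bias = assumed shift × share of pregnancies affected. The standard error is √(2/99) = 0.142 SD. Type I error is the chance that a nominal 5% two-sided test rejects when the only difference is this bias. The article gives no size for an early-pregnancy shift, so a range is shown.

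| Assumed shift | Bias (SD) | Type I error |
|---|---|---|
| 0.25 SD | 0.01 to 0.03 | 5.1% to 5.7% |
| 0.5 SD | 0.02 to 0.07 | 5.3% to 7.7% |
| 1 SD | 0.05 to 0.14 | 6.4% to 16% |

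These figures refer to the two-group comparison behind the sample size, not directly to the risk ratio from the Poisson model.

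**5. Cost of excluding these women.** If they are counted within the 198, about 184 to 193 remain (198 − 13.6 to 198 − 4.9), and power for 0.4 SD is about 77% to 79%.

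**The case against.** The strongest reply is that the protocol's intent is plainly the opposite of keeping these women. Visits are conditional on no conception, pregnancy status is recorded at 3 months, outcomes are described throughout as subsequent, and early conceptions are budgeted as incomplete follow-up. A pregnancy test at the visit, or back-dating from the scan, may well be in the full protocol that this article condenses. These women are trying to conceive, track their cycles and are told to report tests promptly, so long recognition lags are unlikely. The lag and the shift are both assumptions from outside the article.

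Much of this stands. A reader might infer that the plan deliberately retains women who conceived before the visit; the article does not say so, and their inclusion follows only from the rule as written. A reader might also carry the point over to the 6-month trajectory analysis, but that analysis already has a not-conceived condition and needs no more than a clarification. A lag of five weeks would put a woman at about seven weeks of gestation, inside the study's own scan window, so 2 to 4 weeks is the more defensible range.

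What does not stand is that this is merely omitted detail. The article states a rule and asserts that it secures temporal order. Even a test at the visit would miss the most recent conceptions, and the Sample size allowance removes only women who do not attend.

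**Conclusion.** The point holds as a moderate weakness. The entry rule and the outcome window together allow some conceptions that precede the exposure measurement to be counted as following it, so the assurance of temporal order is not met.

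On the protocol's rates and a 2 to 4 week lag, about 5 to 14 women are affected. The resulting bias is negligible if early pregnancy shifts an indicator by 0.25 SD, about 0.02 to 0.07 SD at a 0.5 SD shift, and about 0.05 to 0.14 SD at 1 SD. A reader might infer that reverse causation could by itself produce the planned 0.4 SD difference; these figures do not support that. The article also gives no basis for stating how far, or in which direction, early pregnancy moves any particular indicator. The case for acting is that the error would be systematic, would fall in the primary analysis, and is easy to remove.

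**What to change.** In the Statistical analysis plan section, restrict the primary exposure analysis and the 3-month gene-expression comparison to women with no conception dated on or before their 3-month assessment, and count only conceptions dated after it as events. Date conception from the dating scan or, where there is none, from the recorded last menstrual period and the woman's own cycle length. A fixed interval after the last period would date conception too early in women with long cycles and exclude valid exposures.

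For the trajectory analysis, state only that the existing 6-month condition refers to dated conception, not to known pregnancy status. An optional sensitivity analysis may also drop conceptions dated shortly after the 3-month visit, to allow for dating error.

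The cost is a wording change and one date comparison on data already planned. At most about 5 to 14 women leave the analysis set, with power of about 77% to 79% if they are counted within the 198. On the Sample size accounting, early conceivers are already part of the 30% allowance, so excluding them may simply return the set to 198. No change to enrolment is needed. If the rule is not adopted, the statement that visit completion ensures temporal order should be withdrawn.

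### The month-3 selection check pools women who conceived early with women who did not attend, so its result is hard to interpret; the two should be compared with completers separately

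*Protocol article*

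**What the plan says.** All references are to the Protocol article.

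- **Analysis set.** The Statistical analysis plan section says that "the primary analysis will include only participants who have completed the 3-month visit". The reasons given are that exposure is fully known only for these women and that exposure must come before outcome.
- **Check.** The same section continues: "To identify any potential selection bias, we will compare baseline characteristics between participants included in and excluded from the primary analysis". A further comparison, TEMPO against HELMS alone, concerns entry into TEMPO and not attendance at month 3. The tests are two-sample tests: "We will use Pearson’s chi-squared test for categorical variables and either independent t-test or Mann-Whitney U test for continuous variables".
- **Who is excluded.** The Sample size section allows for a "potential 30% incomplete 3-month follow-up (including an estimated 15% pregnancy rate within 3 months". The Study procedure section schedules the 3-month visit only for women who have not conceived, so early conceivers leave the primary set by design.
- **Adjustment and missing data.** The primary models adjust for covariates chosen from the literature and a directed acyclic graph. For missing values the plan says "Missing data will be handled through multiple imputation", with other options, and adds a sensitivity analysis on complete data.
- **Acknowledged risk.** The Discussion concedes that loss to follow-up may cause selection bias and answers with retention measures.

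**The concern.** The excluded group combines two kinds of women for whom the comparison means different things. Those who conceived before month 3 have already had the outcome. Leaving them out follows from the need for temporal order and only defines the population to which the estimate applies. Those who were not pregnant but did not attend belong to that population and are missing from it. Their absence can bias the risk ratio if attendance depends both on the 3-month change and on baseline factors related to conception.

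A single included-versus-excluded test cannot separate the two. A clear difference may only reflect the intended exclusion of the most fertile women. The absence of a difference may hide two differences of opposite sign. In either case the analyst does not learn which baseline variables predict non-attendance, and those are the variables the adjusted model needs.

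**Working it through.** **1. The plan's own figures.** Inputs from Sample size: effect 0.4 SD, two-sided 5%, 80% power, 50% pregnant, 30% incomplete.
- Per group: 2 × ((1.960 + 0.842)/0.4)² = 98.1, rounded up to 99, so 198 in total. This matches.
- Enrolment: 198/0.70 = 282.9, rounded up to 283. This matches.

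**2. Make-up of the excluded group.**
- Excluded: 283 − 198 = 85.
- Conceived before the visit: 0.15 × 283 ≈ 42.
- Not pregnant and not attending, by subtraction: (0.30 − 0.15) × 283 ≈ 42, which is 0.15/0.85 ≈ 18% of women not pregnant at month 3.
- Early conceivers are 0.15/0.50 = 30% of all expected pregnancies. If 50% holds for the whole cohort, the proportion conceiving later among those not pregnant at month 3 is (0.50 − 0.15)/0.85 ≈ 41%.

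**3. What the check can detect on one baseline variable.** Power ≈ Φ(d/SE − 1.96) + Φ(−d/SE − 1.96), with SE = √(1/n₁ + 1/n₂) in SD units. The differences of 0.4 SD are assumptions; the documents give none.

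| Comparison | Assumed pattern | Difference tested | SE | Power |
|---|---|---|---|---|
| Pooled, 198 vs 85 | subgroups differ by +0.4 and −0.4 | 0 | 0.130 | about 5% |
| Pooled, 198 vs 85 | only one subgroup differs by 0.4 | about 0.2 | 0.130 | 34% |
| Pooled, 198 vs 85 | both differ by 0.4, same direction | 0.4 | 0.130 | 87% |
| Split, 198 vs 42 | that subgroup differs by 0.4 | 0.4 | 0.170 | 65% |

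Simulated t-tests with opposite differences gave pooled rejection of 4.9% at ±0.3 SD and 4.3% at ±0.5 SD. The separate comparisons rejected about 43% and 84% of the time.

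**4. How far the risk ratio could move.** Illustrative simulation among women not pregnant at month 3, all values assumed except the 18%: true risk ratio 1.25 per SD of change; 1.3 to 1.5 per SD of a baseline factor; 18% non-attendance; attendance log-odds 0.8 to 1.1 per SD of each, with no interaction or an interaction of ±0.5.

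| Analysis of completers | Risk ratio per SD |
|---|---|
| Baseline factor not in the model | 1.19 to 1.24 |
| Baseline factor in the model | 1.25 throughout |
| Weighted by attendance probability from the baseline factor only | 1.18 to 1.24 |

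On the log scale a shift from 1.25 to 1.23 is 0.223 − 0.207 = 0.016, and from 1.25 to 1.19 it is 0.223 − 0.174 = 0.049. The standard error at 198 women with 41% pregnant is roughly √(0.59/(0.41 × 198)) = 0.085, or about 0.11 with the model-based Poisson variance.

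**The case against.** The restriction is deliberate, its reason is given, the sample size allows for it and the risk is disclosed. Excluding early conceivers needs no correction. This is also a condensed article. A table split by reason for exclusion, or an extra model, may appear in a full analysis plan that is not shown, and nothing in the text forbids it. These points stand, and they limit the criticism to the check that the article itself specifies.

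A reader might go further and infer that selection bias will pass undetected and that nothing corrects for it. The documents do not support that.
- Exact cancellation needs equal and opposite differences, for which there is no evidence. If both subgroups differ in the same direction, the pooled test is stronger than the split one (87% against 65%).
- The primary models are covariate-adjusted. Where the baseline predictor of attendance is measured and included, the simulated bias disappears. The qualification is that the adjustment set comes from the literature and a graph, so it helps only if it contains the predictors of non-attendance, and the pooled check can fail to show them.

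A reader might also infer that inverse-probability weights from baseline data are the remedy. In the simulation they left the risk ratio essentially where it was, because attendance also depended on the 3-month change, which is unobserved in non-attenders.

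Multiple imputation could be read as covering non-attenders, but the restriction of the primary set to completers leaves it to act only on gaps among them.

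**Conclusion.** The point holds as a defect in a stated method. The check for selection at month 3 treats as one group an approximately even mixture of about 42 intended exclusions and about 42 women whose absence is the actual threat. Its result is hard to interpret either way, and it can hide differences of opposite sign.

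The even split rests on the plan's 30% and 15%, with the remainder obtained by subtraction. Everything about the size of baseline differences and of bias rests on assumed values. Neither the size nor the direction of any bias can be derived from the documents. In the scenarios tried, the shift on the log scale (0.016 for a risk ratio of 1.23, 0.049 for 1.19) is smaller than the standard error, so a modest effect is the reasonable expectation. The change is worth making because it is inexpensive and shows which variables the adjusted model needs.

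**What to change.** 1. Replace the two-group comparison with three groups: completers, women who conceived before the 3-month visit, and women not pregnant who did not attend. Report standardised differences from completers rather than relying on p-values. With 42 against 198, chance alone gives differences up to about 1.96 × 0.170 = 0.33 SD, so small values should not be over-read.
2. State that the primary estimate applies to women not pregnant at 3 months.
3. Pre-specify a sensitivity analysis that adds to the covariate-adjusted primary models the baseline predictors of non-attendance found in step 1, with the rule for selecting them fixed in advance.
4. Optionally add a model weighted by the probability of attendance estimated from baseline variables, as a secondary check only, and say that it does not repair selection that depends on the 3-month change itself.

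The cost is analysis-plan wording and one extra model (two with step 4), with no new data collection. The price is smaller groups per comparison: about 65% power at 0.4 SD for 42 against 198, compared with 87% for the pooled test if both subgroups differ in the same direction.

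### Fecundability risk sets open at study entry although the exposure is only known at the 3-month visit, so about three nearly event-free cycles per woman are counted as at risk

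*Protocol article*

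**What the plan says.** All references are to the protocol article.

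- **Clock.** Under Outcomes and assessments, time-to-pregnancy is the "interval between the date of the last menstrual period at recruitment (baseline) and before conception" (or the last follow-up call), converted to menstrual cycles.
- **Risk sets.** The Statistical analysis plan handles left truncation by "considering only the cycles actively attempted during the study period". Its example is a woman who had tried for four cycles at entry; if she "achieves pregnancy after seven cycles, only the cycles from the fifth to the seventh will be included in the analysis".
- **Exposure.** The same section defines the exposure as "the change in circadian behavior and metabolic health indicators over the first 3 months of the preconception period", and states that "only participants who complete the 3-month assessment have a fully characterized exposure and are included in the primary analysis".
- **Condition for the visit.** Under Study procedure, the 3- and 6-month visits are held only for women who have not conceived. Sample size counts the 15% expected to conceive within 3 months as part of the 30% with incomplete 3-month follow-up.
- **Trajectory analysis.** The exploratory analysis will "include only participants who have not conceived by the 6-month visit" and then relates trajectory groups to fecundability.

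Nothing in the article moves risk-set entry to the 3- or 6-month visit. The restriction to completers decides who is analysed, not which of their cycles count.

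**The concern.** A woman has an exposure value only if she reached the 3-month visit without a known pregnancy. Her cycles before that visit could hardly have produced an analysable event, yet the plan places them in the denominator. This is immortal time.

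The consequences differ by quantity. Any absolute per-cycle fecundability from these data is diluted. For the ratio, the time scale matters. On the cumulative-attempt scale, the event-free early study cycles of a woman who had tried for a long time share risk sets with cycles in which women with shorter earlier attempts really can conceive. If the 3-month change is related to earlier attempt time, the event-free cycles fall unevenly across exposure levels and the ratio shifts.

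The example matters because a programmer would copy it. It counts three study cycles for a woman who, at typical cycle lengths, would have conceived before her 3-month visit.

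**Working it through.** **Plan's own figures.** With 0.4 SD, 80% power and two-sided 5%, n per group = 2(1.96 + 0.842)²/0.4² = 98.1, so 99 per group and 198 in total. Then 198/0.70 = 283. Both stated numbers reproduce, so the accompanying 50% (12 months) and 15% (3 months) are used below.

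**Assumptions not in the document.** Cycle length is 25-35 days, the clock starts at enrolment, the hazard after the visit is constant, and every cycle counts as at risk.

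**Event-free cycles per woman** = 91.3 days / cycle length: 3.65 (25 days), 3.26 (28), 3.04 (30), 2.61 (35).

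**Share of person-cycles, 28-day cycles.**

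- Risk after the visit: p = (0.50 - 0.15)/0.85 = 0.412; 198 × 0.412 = about 82 events.
- Cycles from month 3 to month 12: m = (365.25 - 91.3)/28 = 9.78.
- Per-cycle hazard: f = 1 - (1 - 0.412)^(1/9.78) = 0.053.
- Cycles truly at risk: p/f = 7.80 per woman, about 1,544 for 198 women.
- Event-free cycles: 3.26 × 198 = about 646.
- Share: 646/(646 + 1,544) = 29.5%.
- Fecundability: 82/1,544 = 0.053 with entry at the visit, against 82/2,190 = 0.037 with entry at enrolment, about 30% lower.

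Across cycle lengths of 25-35 days the share stays at 29-30%. It is about 31% if 50% of completers conceive after the visit, as the 99:99 split implies.

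**Fecundability ratio.** Discrete-time complementary log-log model with attempt-cycle indicators, simulated with an assumed mean earlier attempt of about 3.5 cycles. Ranges are from separate runs.

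| Correlation of change with earlier attempt time | True ratio | Entry at enrolment |
|---|---|---|
| 0 | 1.25 | 1.24 |
| +0.3 | 1.00 | 0.93 |
| +0.3 | 1.25 | 1.14-1.16 |
| -0.3 | 1.00 | 1.07-1.09 |
| -0.3 | 1.25 | 1.31-1.34 |

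At zero correlation a true 1.00 stays at 1.00. Entry after month 3 returned 1.00-1.02 and 1.23-1.26 for true values of 1.00 and 1.25. A different assumed dependence (binary exposure, mean earlier attempt 2.6 against 4.3 cycles) turned a true 1.00 into about 1.13 if exposed women had tried for less time, and about 0.88 if longer. So the size depends on the dependence assumed. Keeping entry at enrolment but adding earlier attempt duration as a covariate brought a true 1.00 back to 0.99-1.00.

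**The example.** Three 28-day cycles end at day 84, with ovulation near day 70. The 3-month visit falls near day 91, so this woman would usually have no 3-month change. At 35 days the third cycle ends at day 105, with ovulation near day 91, so she might.

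**Trajectory analysis.** 182.6/28 = about 6.5 event-free cycles per woman, if the same entry rule is used.

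**The case against.** The strongest reply is that the plan estimates a ratio. Every analysed woman carries much the same event-free stretch, so it is non-differential unless exposure is related to earlier attempt time. The document gives no such correlation. Covariates are to be chosen from the literature and a directed acyclic graph, and may include earlier attempt time, which would largely remove the distortion. All of this stands. It limits the consequence but does not justify the entry rule.

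Four stronger readings are tempting and not supported:

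- **That the ratio itself is about 30% too low.** That figure applies only to absolute fecundability, which the plan does not list as a model result.
- **That the plan breaks its own temporal ordering.** Restricting to completers already puts nearly every analysed event after the exposure window. Extra event-free cycles do not reverse that order.
- **That the woman in the example could never be analysed.** The example is there to show why pre-study cycles are dropped. With long cycles, or a cycle without intercourse that is not counted, her third cycle at risk could extend past the visit.
- **That moving entry costs no events.** Starting at the first cycle that begins after the visit would discard the cycle in progress. At 28 days that cycle holds about 198 × 0.053 = 10 conceptions, roughly 5 of them after the visit if half the women ovulate later.

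It may also be said that the completer restriction is worded for the primary analysis. The fecundability model uses the same 3-month change, so the condition carries over.

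**Conclusion.** The point holds for risk-set entry in the secondary fecundability analysis. As written, about three nearly event-free cycles per woman, 29-31% of person-cycles, are counted as at risk. They are nearly rather than strictly event-free, because a woman with an undetected conception could still attend the visit. Three is towards the upper end for women with cycles not counted for lack of intercourse.

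Absolute fecundability is understated by about 30%, given the protocol's 50% and 15% and a constant hazard after the visit. Bias in the ratio is conditional: it needs the 3-month change to be related to earlier attempt time and that time to be left out of the model. Whether either holds cannot be told from the article.

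This should be fixed before analysis, but it does not threaten the primary analysis: the modified Poisson model uses no cycle risk sets. The trajectory analysis is exploratory, and its entry rule is not stated separately.

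**What to change.** 1. Keep cumulative attempt cycles as the time scale and set delayed entry at the 3-month visit. Count the cycle in progress if the visit precedes its estimated ovulation; otherwise start at the next cycle.
2. Treat conceptions dated before the visit as not eligible for this analysis.
3. Apply the same rule at the 6-month visit in the trajectory analysis.
4. Replace the example with one whose conception follows the visit. For instance, take a woman with four cycles tried at entry, 28-day cycles and a visit on day 91. The visit falls 7 days into attempt cycle 8, before ovulation near day 98. If she conceives in cycle 10, cycles 8 to 10 count; had the visit followed ovulation, only 9 and 10 would.
5. Describe the estimate as conditional on not being pregnant at 3 months.

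The cost is one entry-time definition and some wording. No new data are needed, since menstrual cycles are already tracked. A few conceptions around the visit may be dropped, and ovulation dates will be estimates.
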